### Power and sample size estimation

Because there are currently no effect sizes for extensive paper-and-pencil-based preoperative cognitive training in cardiac surgical patients using extracorporeal circulation, and because their influence on the incidence of POD and POCD is unclear, we have estimated sample size based on the effect sizes of general cognitive training in older healthy individuals, which ranges between d = 0.4 and d = 0.9 (20, 21). To not underestimate or overestimate the required sample size, we use an average value of d = 0.65. To find an effect size of d = 0.65 at a test power of 0.8 (alpha = 0.05) within an ANCOVA, a sample size of 77 subjects is required. With an estimated dropout rate of 23% in the preoperative test phase, the total sample size will be 100 subjects. The sample size per group is thus 50 patients. We used the analysis software G^*^Power-3 to calculate the sample sizes and the statistical power (22). We want to note that the power analysis refers to our secondary outcome “Changes from baseline neuropsychological parameters at the end of cognitive training.” Accordingly, the primary outcomes regarding the incidence of POD and POCD will be calculated exploratively.

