	Cognitive flexibility	TMT-B (speed)	Linking numbers and letters in alternately order (seconds)
	Inhibition	SKT-7	Naming interfering letter, e.g., “S” instead of “T” (seconds)
Language	Word fluency	RWT (phonetic)	Naming words with specific initial letter (number of correct items)
		RWT (semantic)	Naming words from a specific category (number of correct items)
Perceptual motor	Visuo-construction	MOCA (3-D figure)	Drawing a 3-D figure (number of correct items)

BVMT-R, Brief Visuospatial Memory Test-Revised; VLMT, Verbaler Lern- und Merkfähigkeitstest (Auditory Verbal Learning and Memory Test); TMT, Trail Making Test; LNS, Letter Number Span; SKT, Syndrom-Kurztest Test (Short Performance Test); RWT, Regensburger Wortflüssigkeits-Test (Regensburger Word Fluency Test); MOCA, Montreal Cognitive Assessment.

Analyses of covariance (ANCOVAs) will be conducted to determine the effects of cognitive training on each neuropsychological parameter, CFQ, SF-36, and HADS-D. In the ANCOVA, the postoperative test value will be the dependent variable, groups will be the fixed factor, and the preoperative test value will be the covariate. Confounder variables that could affect the results will be implemented in addition to the preoperative cognitive values as further covariates to the ANCOVA. Confounder variables are defined as whether a correlation analysis among demographic variables, perioperative details, and neuropsychometrical changes between pre- and postoperative testing is significant.

Assumptions for ANCOVAs will be tested using a visual inspection of QQ and distribution plots of the dependent variable for normality, the Levene test for variance-homogeneity of the dependent variable, and a statistically significant correlation between the dependent variable and covariate (preoperative test value) calculated with Pearson's product–moment correlation. When assumptions for the ANCOVA are violated, difference values between pre- and post-tests will be calculated, followed by Mann–Whitney U-tests for between-subject effects. The effect sizes of continuous results will be given in η2.

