In addition to altering preoperative cognitive performance to potentially counteract POD and POCD, other risk factors regarding POD such as poor sleep burden (50) and heart rate response/recovery to exercise (51) can also be modified in the preoperative setting and may be linked to preoperative risk factors such as depression and reduced cognitive functions.

Should it become evident that the use of our cognitive training can both reduce the incidence of POCD and POD and improve health-related quality of life, one possibility could be to integrate this intervention into a standardized prehabilitation program. It can also be evaluated in other patient populations affected by postoperative neurocognitive dysfunctions.

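### The 80% power holds for one ANCOVA on one parameter, but the plan assigns it to an outcome tested on 15 parameters with none named as key

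*Protocol article*

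**What the plan says.** All references are to the protocol article.

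- **Power and sample size estimation.** The effect size is the midpoint of a range of 0.4 to 0.9 from training studies in healthy older people: "we use an average value of d = 0.65". The calculation is stated for a single test, "To find an effect size of d = 0.65 at a test power of 0.8 (alpha = 0.05) within an ANCOVA", and gives 77 subjects. Dropout of 23% brings the total to 100, 50 per group. The section says that this calculation refers to the secondary outcome on change in neuropsychological parameters at the end of training. It adds that "the primary outcomes regarding the incidence of POD and POCD will be calculated exploratively".
- **Planned statistical analyses.** ANCOVAs are run to "determine the effects of cognitive training on each neuropsychological parameter", and also for CFQ, SF-36 and HADS-D. Table 2 lists 15 parameters in 12 subdomains: BVMT-R 3, VLMT 5, TMT-A 1, LNS 1, TMT-B 1, SKT-7 1, RWT 2 and the MOCA figure 1. None is singled out. POD and POCD are compared by chi-square or exact test, with odds ratios and 95% confidence intervals.
- **Abstract and Introduction.** The effect on POD and POCD incidence is the primary objective.
- **Abstract (Discussion) and the closing paragraph of the Discussion.** A possible place in a prehabilitation programme is raised on this condition: "Should it become evident that the use of our cognitive training can both reduce the incidence of POCD and POD", together with better quality of life.

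**The concern.** A power statement belongs to a test. Here it is stated for one ANCOVA and attached to an outcome that the analysis section splits into 15. A reader of the eventual report could not tell which of the 15 results is the one for which the trial was sized. If any significant parameter can be presented as the powered training effect, the 5% error rate in the sample size section no longer describes that claim. If alpha is instead shared over the 15, the 80% no longer describes it.

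The label secondary does not remove the problem. Since the primary outcomes are exploratory, this is the only outcome with a power calculation and so the trial's de facto confirmatory question. At the same time the objective and closing statements still rest on POD and POCD, for which no detectable difference is given.

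**Working it through.** **1. The plan's own figure.** Inputs from the sample size section: d = 0.65, alpha 0.05, power 0.80, two groups; one covariate (the baseline value) from the analysis section. For an ANCOVA F test, f = d/2 = 0.325, λ = f²N, df = (1, N − 3).

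- N = 76: power 0.798.
- N = 77: λ = 0.1056 × 77 = 8.13, critical F = 3.97, power 0.804.
- Dropout: 77 / (1 − 0.23) = 100.

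Both stated numbers reproduce. One parameter tested alone at 0.05 has the stated power.

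**2. False positives over 15 parameters, each at 0.05.** The per-test level is inferred from the only alpha that the article gives. With independent tests, 1 − 0.95¹⁵ = 0.537. For equally correlated normal test statistics (the correlation is an assumption; the article gives none):

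| Inter-test correlation | Chance of at least one false positive |
|---|---|
| 0 | 54% |
| 0.3 | 46% |
| 0.5 | 36% |
| 0.7 | 26% |

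Independence is implausible, since five parameters come from the VLMT and three from the BVMT-R. Even the lowest entry is about five times 5%.

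**3. Power if alpha is split.** 0.05/15 = 0.00333, critical F(1, 74) = 9.20, λ still 8.13: power 0.434 per parameter. For 80%, 140 evaluable would be needed, or 140/0.77 = 182 in total.

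This takes d = 0.65 as the covariate-adjusted effect, as the plan's 77 does. If d is on the raw scale, the adjusted effect is d/√(1 − r²), with r the baseline correlation (assumed):

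- r = 0.5: 0.65/0.866 = 0.75, power 60%.
- r = 0.7: 0.65/0.714 = 0.91, power 83%.

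**4. What the exploratory primary outcomes can show.** Rates come from the Introduction: POCD 28% in months one to four, POD 14% to 50%. Halving is an assumed effect. Exact two-binomial power, uncorrected chi-square at 0.05, with the 77 evaluable split 39/38:

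| Comparison | Power |
|---|---|
| POCD 28% vs 14% | 32% |
| POCD 28% vs 5% | 82% |
| POD 14% vs 7% | 16% |
| POD 50% vs 25% | 64% |

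With all 100 patients evaluable, halving POCD has 41%.

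**5. A broad composite as the key test.** Six of the 12 subdomains are visual or verbal memory, whereas the Cognitive training section targets word fluency, working memory, attention and planning. Suppose that d = 0.65 holds in 4 of 12 subdomains and is zero elsewhere, with inter-subdomain correlation 0.3 (all assumed). The mean effect is 0.65 × 4/12 = 0.217. The SD of the mean of 12 is √((1 + 11 × 0.3)/12) = 0.599. The composite effect is 0.217/0.599 = 0.36, and power at N = 77 is about 35%.

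**The case against.** **The design still has its stated power.** A reader might infer that it has 80% power for no claim at all. That does not follow. Each parameter taken alone at 0.05 has 80.4%, and if all 15 effects were 0.65 the chance of at least one significant result would exceed 98% even at correlation 0.7. Unadjusted testing inflates the type I error; it does not lower power. The 43% arises only under a correction that the article does not mention.

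**A chance finding is not certain.** A reader might also infer that some parameter will probably be significant by chance. Only near-independence takes the figure above one half.

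**The primary outcomes' status is disclosed.** This is correct. The sample size section says so plainly, and the analysis section already commits to odds ratios with confidence intervals. The closing statements are tentative, do not mention significance and also require better quality of life. They are not a decision rule and should not be read as one. What remains is a mismatch: the same outcomes are the primary objective in two places and exploratory in a third.

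**Multiplicity may be handled in an analysis plan that is not shown.** This is possible, and the absence of a rule from an article is not the point. The point is that 77 was derived at an unadjusted 0.05 for an outcome that the article itself splits into 15. A Bonferroni rule elsewhere would undercut the published power on the article's own assumptions.

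**Conclusion.** The concern holds in a limited form. The sample size arithmetic is correct for one ANCOVA on one pre-named parameter, but the article names no such parameter and attaches the figure to 15 separate tests. Followed as written, the only powered outcome carries a false-positive chance of about 26% to 54% across its parameters, depending on an assumed inter-test correlation of 0.7 down to 0. Sharing alpha by Bonferroni would leave about 43% power per parameter, or 60% to 83% on the raw-scale reading with an assumed baseline correlation of 0.5 to 0.7.

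The low power of the POD and POCD comparisons is not a hidden error. It is a consequence of their exploratory status that the objective and closing statements do not yet reflect. This should be corrected, but it does not invalidate the design.

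**What to change.** 1. Before any unblinded result is seen, interim looks included, name one key test of the training effect: the admission value (t3 in Table 1) by group, adjusted for the first-assessment value (t0). It may be a single parameter or a Z-score composite, for example of the functions that the training targets. In a composite, reverse the sign of the tests scored in seconds (TMT-A, TMT-B, SKT-7).
2. Attach the 80% power statement to that test only.
3. Report the remaining parameters with Holm adjustment, or label them descriptive.
4. Align the objective in the Abstract and Introduction, and the closing statements in the Abstract and Discussion, with the exploratory status of POD and POCD. State what the sample can show: with 39/38 evaluable, about 32% power to halve POCD from 28%, and about 16% to 64% to halve POD over the article's range.

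**Cost.** Protocol wording, an amendment to the ethics committee and at most one derived variable; no extra patients. Individual parameters lose confirmatory status. A composite over all 12 subdomains risks dilution, as in step 5 of the working, so the choice should follow the functions that the training is expected to change.

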### Metric assessments

Cognitive tests will be performed by a neuropsychologist 2–3 weeks before surgery, at admission to the acute clinic, during postoperative stays in intensive care and the normal ward, at discharge from the cardiac surgery clinic, and 3 months after surgery. Parallel test forms will be used in the follow-up examinations to account for individual learning effects. Parallel test forms will be counterbalanced for each test time point.

#### Objective cognition

The cognitive test battery measures verbal and visual memory with immediate-, free recall-, and recognition conditions, selective attention, verbal working memory, cognitive flexibility, inhibition, word fluency, and visuoconstruction.

With the German-validated version of the Montreal Cognitive Assessment (MOCA) (23), cognitive functions such as visuoconstructive ability, object naming, verbal memory, working memory, attention, phonematic word fluency, abstraction, cognitive flexibility, and orientation are assessed within the framework of a 10-min screening procedure (23).

Verbal memory will be assessed using the Verbaler Lern- und Merkfähigkeitstest (VLMT), a modified German version of the Rey Auditory Verbal Learning Test (24). This test can be used to evaluate immediate-, free recall-, and recognition conditions. Between the short-delayed and longer-delayed verbal episodic memory recall, non-verbal cognitive tests are performed to avoid possible effects of interfering words not included in the learned word list.

With the Letter–Number Test (LNS), the verbal working memory will be tested. The patient is supposed to rearrange a mixed sequence of letters and numbers through mental reorganization in such a way that first all numbers and then all letters are to be named in ascending order (25).

Visual memory will be examined with the Brief Visuospatial Memory Test-Revised (BVMT-R) (26). In the BVMT-R, the patient is shown six geometric figures for 10 s on a DIN A4 sheet of paper, which are to be drawn directly afterward. This procedure is repeated with the same figures in a total of three learning trials. The figures are to be freely replicated in a time-delayed episode with the following recognition help.

Selective attention will be examined using the Trail Making Test A (TMT-A), for which three validated parallel test versions are available (27). In the TMT-A, the patient has to connect numbers in ascending order on a test sheet as fast as possible.

Cognitive flexibility will be measured by the Trail Making Test B (TMT-B) (27) and cognitive inhibition by a subtest of the Syndrom-Kurz Test (SKT-7) (28). With the TMT-B, the patient's task is to connect numbers and letters alternately in ascending order. In the SKT-7, the patient has to rename a series of letters (e.g., “S” instead of “T,” and vice versa).

The semantic-categorical word fluency is tested with the Regensburger Wortflüssigkeits-Test (RWT) (29). In this test, the patient has to name in 1 min as many words as possible from a certain category.

#### Subjective cognition

Study patients will be asked to complete a validated German 25-item version of the Cognitive Failures Questionnaire for Self-Assessment (s-CFQ) (30). Because memory disorders play an important role in the everyday functions of patients, the s-CFQ was modified with four additional questions related to memory failures, taken from the validated German version of the Memory Complaint Questionnaire (31). Close relatives of the patients will also be asked to answer an eight-item cognitive questionnaire for external assessment (f-CFQ) with regard to the patients (32). All have to be answered on a 5-point scale from “never” to “very often.” The purpose of these questionnaires is to investigate the frequency of failure in daily living in terms of memory, attention, action, and perception in the past 3 months.

#### Cognitive reserve/cognitive everyday activities

The Lifetime of Experiences Questionnaire (LEQ-D), which has been translated and validated into German, is intended to determine the cognitive reserve in 34 items for three areas of life: education, occupation attainment, and lifestyle activities (33). These relate to early-, midlife-, and late-life reserve measures. Because the LEQ-D records the cognitive everyday activities unspecifically for the time immediately before surgery, the cognitive activity scale (CAS) according to Tow et al. (12) will also be used. This scale covers 12 cognitive activities, such as reading the newspaper, solving crosswords, writing, or group meetings, related to the previous week.

#### Delirium

Postoperative delirium will be examined during the stay in the intensive care unit with the German-validated Intensive Care Delirium Screening Checklist (ICDSC) (34). To be able to record the status of POD with high sensitivity and specificity, even during the stay in the normal ward, a newly developed version of the Confusion Assessment Method (3D-CAM) validated in German will also be used (35). Both tests record the clinical symptoms of consciousness, attention, orientation, hallucinations, psychomotor retardation or agitation, speech, and changing symptoms by observing behavior and asking concrete questions to the patient. The ICDSC also documents disturbances in the sleep–wake rhythm.

#### Depression and anxiety

Patients assessed their recent (prior week) depressive and anxiety symptoms using the validated German version of the Hospital Anxiety and Depression Scale (HADS-D) (36). Each scale contains seven questions to be answered by the patients.

#### Health-related quality of life

Health-related quality of life will be assessed with the 36-Item Short Form Health Survey (SF-36, Version 1.0) (37). The SF-36 includes 36 items covering eight health-related factors, including physical functioning (10 items), role limitations due to physical health (four items), role limitations due to emotional problems (three items), energy/fatigue (four items), emotional wellbeing (five items), social functioning (two items), pain (two items), and general health (five items). Furthermore, we will determine a total score across all eight factors, as well as a two-factor model, indicating the physical state of health (physical functioning, role limitations due to physical health, pain, and general health) and psychological state of health (role limitations due to emotional problems, energy/fatigue, emotional wellbeing, and social functioning). The answers provided by the patients within the factors refer to the last 4 weeks, except for the factor physical functions and the first question of the factor general health, which refer to the present state of health. Furthermore, it also contains a single item (item 2, health change), which indicates the extent to which the present health has changed in relation to the past year. The SF-36 will be scored using the RAND scoring method (38). Each item in the questionnaire is assigned a score from 0 to 100, with a higher score indicating a better health state.

For the CFQ, MCQ, and SF-36, missing data will be handled as follows. If the patients answered at least 50% of all items per factor and time point, the mean score of this factor will be calculated to determine the values of the factors. Items left blank (missing data) will not be considered. Therefore, the factor values will represent the average for all items of a factor that the respondent responded to.

### Data management

All personal data about recruited patients will be subject to medical confidentiality. Paper-based assessment forms will be used to record all variables. The data will be entered into an electronic database, which will be password-protected and double-checked for accuracy. All signed informed consent forms, assessment forms, and the randomization list will be stored in locked cabinets. Each patient will receive a sequential number recorded on the paper-based assessment forms and in the electronic database. Personal data such as first name, last name, and address will not be included in the paper-based assessment forms or the electronic database.

### Cognitive training

We have validated a postoperative paper-and-pencil-based cognitive training program for older cardiac-surgery patients with the effect of reduced POCD at discharge from rehabilitation (after 3 weeks of training) and at a 3-month follow-up (39). In the INCORE study, we will use this training program for the preoperative setting. Here, we will provide information about the concept of our training.

We derived the design of our cognitive training program using the German language-validated, paper-and-pencil-based intervention by Müller et al. (40). This program is intended to train working memory, cognitive flexibility, word fluency, and planning skills. To achieve better patient acceptance, we only adopted exercises that we found most useful and combined them with new tasks developed by our group. Furthermore, we initially constructed our training to address several cognitive functions that are particularly important in everyday life to maintain social functions and earning capacity. These include word fluency, working memory, attention, and the ability to plan. One training unit will last approximately 40 min and will be conducted for 2–3 weeks, about 6 days a week. The daily training program consists of eight different types of standardized tasks related to the processing of words, categories, images, mental arithmetic, and planning. On each training day, new words, categories, images, head calculations, and planning tasks will be presented. Each task takes between 2 and 10 min to complete. To manage their working time, the patients must use a digital clock. If the patient has any questions about the tasks, they can contact the training supervisor by telephone. In addition, the training supervisor will call the patient once a week to monitor cooperation. Each task contains precise written instructions that may be helpful in the execution. Patients will also be told that their exercise solutions will not be corrected. Therefore, it does not matter whether the solutions are right or wrong. In this way, we can avoid any possible pressure to perform and patients looking for the right solutions at home. The different types of tasks are presented in the following standardized order.

#### Phonetic word fluency

The patient receives three letters on a sheet of paper. The task is to note as many words as possible that begin with these letters within 2 min. This task is mainly used to train word fluency and was adapted from the work of Müller et al. (40).

#### Categorical word fluency

In this task, the patient receives three different categorical terms on a sheet of paper. The task is to find and note as many words as possible within 2 min that can be assigned to these categories. This task serves mainly to train word fluency and was adapted from the work of Müller et al. (40).

#### Picture stories

The patients receive four to five popular German picture stories by German illustrators such as Wilhelm Busch, Erich Ochser, or Hans Juergen Press, with 3–16 pictures of a story in mixed order. Within 5 min, the pictures have to be arranged mentally in a meaningful order. The newly invented order is to be documented by numbering the pictures with a pen. This task is mainly intended to train working memory and was created by our group.

